#### 2.3.7. Inflammatory Markers

Plasma concentrations of IL-6 and TNF-α will be measured by ELISA kits using an automated analyzer system (Triturus, Grifols, Barcelona, Spain). IL-6 will be evaluated by means of Quantikine immunoassay kit from R&D Systems (Minneapolis, MN, USA). Serum levels of TNF-α will be evaluated using high sensitivity commercial ELISA with an alkaline phosphatase signal amplification system (Quantikine HS, high sensitivity, R&D Systems, Minneapolis, MN, USA).

#### 2.3.8. Genetic Analyses

With the purpose of evaluate the influence of the genetic make-up in adiposity and metabolic changes after interventions, two common single nucleotide polymorphisms related to obesity (rs9939609, *FTO*) and lipid metabolism (rs1799883, *FABP2*) will be detected by Taqman probes (Applied Biosystems, Foster City, CA, USA) through a RT-PCR system.

### 2.4. Allocation and Sample Size

The initial allocation will be performed in such a way that each group had almost the same proportion of *S. maxima*:placebo (1:1) supplemented individuals through the RandomizeR package of the R version 4.0.2 statistical software [34]. Participants’ group allocations will be performed by an independent researcher, who does not have any other involvement during the study, break of double-blind (participants and principal investigators) can occur only in exceptional circumstances and must be immediately reported. Sample size was calculated considering a level of significance of 0.05 with a study power of 0.85, selecting a sample of ≥52 participants. The statistical software G*Power (v3.1.9.7, Universität Kiel, Düsseldorf, Germany) [35] was used to determine the sample size.

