Therefore, we hypothesize that the administration of *S. maxima* alone or together with an exercise plan will decrease the body fat percentage and blood lipids while increasing physical function in sedentary elderly patients with excessive body mass in a randomized, double-blind, counterbalanced, crossover, controlled trial. The main objective of our research is to evaluate the independent and synergistic effect of 12 weeks of *S. maxima* intake (compared to placebo), with or without an exercise program on the body composition (body fat percentage, muscle mass percentage, and body mass index (BMI)) in sedentary older adults with excessive body mass. The secondary objective is to test the effects of both interventions in the blood lipid profile, energy intake, physical function, sleep wake patterns, mental health, and inflammation, as well as to analyze the influence of the genetic background in all outcomes in older adults with excessive body mass.

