### 2.1. Eligibility Criteria

Fifty-two sedentary (daily energy expenditure <4 METs, as measured by a continuous physical activity questionnaire (IPAQ)) [20] older adults (≥60 years) with a BMI over 25 kg/m^2^ volunteered to participate will be recruited by personalized interviews including a Physical Activity Readiness-Questionnaire for Everyone (PAR-Q+) [21] conducted to ensure eligibility. The participants inclusion and exclusion/elimination criteria are depicted in Table 1.

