### 2.2. Interventions

The clinical trial consists of two interventions: (1) supplementation with *S. maxima* (5 g/day) or placebo (5 g/day of a low-calorie saccharine), and (2) an exercise program, during a period of 24 weeks in a randomized, double-blind, counterbalanced, crossover, controlled trial with a 2 × 2 factorial design. Presentation of both supplements will be powder encapsulated in dark capsules of 0.5 g to present the same organoleptic attributes and mask their individual characteristics.

Inclusion in the exercise program intervention will be decided by each participant, who will be randomly assigned to one of the two possible nutritional interventions (*S. maxima* or placebo) categorized into four treatments: an exercise program plus *S. maxima* intake; exercise with placebo administration; *S. maxima* intake without exercise, or placebo supplementation without exercise program (Control). To assess compliance to the supplement intake, a crossover will be conducted for the supplementation interventions.

The first period of treatment will be carried out for 12 weeks, followed by a four-week wash-out period to avoid any possible delayed effect of *S. maxima* in the organism. Finally, a further 12 weeks of treatment for the second intervention groups (Figure 1).

Due to absence of data related to wash-out and treatment periods length, we considered 4 and 12 weeks, respectively, as stated by a systematic review of clinical trials that used spirulina as treatment [22].

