## Figures and Tables

**Figure 1 ijerph-18-01605-f001:**
[figure not shown]
Flow diagram of the experimental design for the impact of *Spirulina maxima* intake and exercise (SIE) trial. Same color indicates the same group of participants.

**Table 1 ijerph-18-01605-t001:** Inclusion and exclusion/elimination criteria to participate in the *Spirulina maxima* intake and exercise (SIE) randomized controlled trial.

Inclusion Criteria	Exclusion/Elimination Criteria
Man or woman	Drinking alcohol
≥60 years	Taking drugs or diet supplements
Daily energy expenditure <4 metabolic equivalents	Presenting an impediment to practicing regular physical exercise
Body mass index≥ 25 kg/m^2^	Participate in any other interventional study
Signed informed consent	<80% attendance to exercise sessions
	Being unhealthy due pre-intervention test results by certified doctor’s decision
	Fracture or surgery in the last six months
	Presenting a chronic disease
	Present a risk when increasing exercise level and/or engage in fitness testing (Physical Activity Readiness-Questionnaire for Everyone (PAR-Q+) with at least one “yes” answer in any of seven pre-screening questions and at least one “yes” in one of the next 10 follow-up questions) [21]

**Table 2 ijerph-18-01605-t002:** Summary of the independent and dependent variables of the *Spirulina maxima* intake and exercise (SIE) randomized controlled trial.

Independent Variables	Dependent Variables
*Spirulina maxima* intake intervention	Body composition (body fat percentage, muscle mass percentage, and body mass index)
Exercise program intervention	Energy intake (total calories, proteins, carbohydrates, fat, and micronutrients consumption)
Wash-out period	Physical function (grip strength and functional physical condition)
Genetic markers	Blood lipid profile (TC, HDL-C, LDL-C, and TG)
	Mental health (anxiety, depression, and cognitive performance)
	Sleep-wake patterns
	Inflammatory markers (IL-6 and TNF-α)

TC: Total cholesterol; HDL-C: High-density lipoproteins associated cholesterol; LDL-C: Low-density lipoproteins associated cholesterol; TG: Triglycerides.

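### The stated power of 0.85 allows for no losses from the 52 recruited, and it is not tied to the synergy part of the main objective

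*Protocol article*

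**What the plan says.** Section 2.4 of the protocol article gives one power statement for the whole study: "Sample size was calculated considering a level of significance of 0.05 with a study power of 0.85, selecting a sample of ≥52 participants". It adds that G*Power "was used to determine the sample size".

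The recruitment target in section 2.1 is the same number: "Fifty-two sedentary (daily energy expenditure <4 METs". The abstract also gives 52.

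Table 1 lists "<80% attendance to exercise sessions" among the exclusion/elimination criteria. Section 2.5 schedules measurements on days 0, 84, 112 and 196.

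The main objective, in section 1, covers both separate and joint effects: "The main objective of our research is to evaluate the independent and synergistic effect of 12 weeks of" *S. maxima*, with or without exercise. On the exercise factor, section 2.2 says: "Inclusion in the exercise program intervention will be decided by each participant". On the supplement, it says that "a crossover will be conducted for the supplementation interventions".

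Section 2.6 plans a repeated measures ANOVA with two times and four treatments, the treatments being treated as between-participant.

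**The concern.** Two things do not fit together.

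First, the number needed equals the number recruited. An attendance criterion can act only after enrolment, so the plan foresees removing people from a sample that has no reserve. The trial runs 28 weeks (12 + 4 + 12), which also leaves time for ordinary withdrawal.

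Second, a single study power is quoted beside a main objective that includes synergy. The power of a supplement by exercise contrast depends on how many participants choose exercise, and the investigators do not control that number.

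The stake is interpretation. A reader who sees 0.85 and then a non-significant synergy result may take it as a well-powered negative. The article does not support that reading unless synergy was the contrast calculated, the split came out as assumed and nobody was lost.

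**Working it through.** **Inputs from the article.** Alpha 0.05, power 0.85, N = 52 (section 2.4); 52 recruited (section 2.1); four treatments and two times in the main ANOVA (section 2.6); supplement crossed over within participants and exercise chosen by the participant (section 2.2).

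**Assumptions.** Tests are two-sided or F tests. The 52 is the uninflated minimum for one test. Losses are 10% (52 × 0.9 = 46.8, taken as 47) and 20% (52 × 0.8 = 41.6, taken as 42). Exercise splits are 26/26, 36/16 and 40/12. The article states neither loss rates nor splits.

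**Step 1: the stated figure.** It cannot be reproduced from the article, which gives no effect size, correlation or test. As a plausibility check, the planned 4 × 2 ANOVA with an assumed f = 0.25 and correlation 0.5 has power 0.840 at N = 52. The stated 0.85 is therefore plausible, and no arithmetic error is shown.

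**Step 2: power after loss.** For each candidate test, find the effect that gives exactly 0.85 at 52, then recompute with fewer participants. These effects are only a device for the check.

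- Paired: noncentrality d√n, n − 1 df. Back-solved d = 0.424.
- Two equal groups: noncentrality d√(n₁n₂/(n₁+n₂)), n − 2 df. Back-solved d = 0.847.
- 4 × 2 ANOVA, group by time: λ = f²·N·2/(1 − ρ), with 3 and N − 4 df. Back-solved f = 0.253 at ρ = 0.5. A different ρ changes f but not the powers below, because λ at 52 is fixed by the 0.85.

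| Test | n = 52 | n = 47 | n = 42 |
|---|---|---|---|
| Paired | 0.85 | 0.81 | 0.76 |
| Two-group | 0.85 | 0.81 | 0.76 |
| 4 × 2 ANOVA | 0.85 | 0.80 | 0.75 |

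The result hardly depends on which test was used, so the missing inputs do not matter much here.

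**Step 3: synergy.** In the crossover, the interaction compares the within-person difference (*S. maxima* minus placebo) between exercisers and non-exercisers. It is a two-sample t test with noncentrality d√(n₁n₂/52) and 50 df. The factor n₁n₂/52 is 13.0 at 26/26, 11.1 at 36/16 and 9.2 at 40/12.

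| Premise | 26/26 | 36/16 | 40/12 |
|---|---|---|---|
| Interaction itself powered at 0.85 for an even split (d = 0.847) | 0.85 | 0.79 | 0.71 |
| Supplement main effect powered at 0.85, interaction of the same size (d = 0.424) | 0.32 | 0.28 | 0.24 |

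The first row has an interaction twice the size of the second (0.847 / 0.424 ≈ 2). All entries assume full retention.

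**The case against.** The strongest reply is that no synergy shortfall has been shown. A reader might infer from the second row of the synergy table that the trial is badly underpowered for its main objective. The article does not support that. The row needs two premises that it does not state: that a paired supplement contrast was the one powered, and that the interaction is no larger than that effect. Section 2.6 does not plan that paired contrast; its paired t-tests compare values before and after treatment. If the supplement worked only with exercise, the interaction would be twice the average effect and would have 0.85 at an even split. If 52 came from a parallel four-group calculation, a crossover analysis using both periods could exceed 0.85. This part of the objection stands.

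A reader might also infer that three primary measures cut the power. That happens only if alpha is divided among them, which the article does not say. Without a division, the power of each test is unchanged and the question is one of type I error.

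It is also fair that a journal article may leave the effect size, test and correlation to the full protocol. Their absence is not the point here.

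On loss, one can reply that section 2.4 gives 52 as a minimum, that the attendance rule can affect only those who choose exercise, and that the article's discussion of limitations explains self-selection as a way to limit desertion. That shows retention was considered. It does not create a reserve, because the stated target is still 52.

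**Conclusion.** The point holds in a limited form. Given that 52 is the uninflated minimum, 0.85 is a zero-loss figure. Power is about 0.80 to 0.81 at 10% loss and 0.75 to 0.76 at 20% loss. The direction is certain, and the size depends on the assumed loss rates but barely on the test.

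The figure is also a single-test figure with no stated link to synergy. What it means for synergy is conditional: from 0.85 down to 0.71 across the splits shown if the interaction was the contrast calculated, and about 0.32 to 0.24 if a crossover main effect was calculated and the interaction is only that large. The article does not say which applies, so it cannot be concluded that the design misses 0.85 for synergy, only that 0.85 cannot be claimed for it as written.

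**What to change.** Restate section 2.4 from the sponsor's own G*Power inputs, not from the effects back-solved above:

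1. Name the test to which 0.85 belongs. Give its power at 52 completers and at the number expected after elimination and withdrawal.
2. Say that 0.85 is not claimed for the supplement by exercise interaction unless that was the contrast calculated, and then only for the assumed exercise split.
3. State that synergy will be reported as an estimate with its confidence interval, so that a null result is not read as a well-powered negative.

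This needs no added enrolment. The cost is a limited rewording and a stated power that looks less favourable.

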### 2.5. Data Collection

Eligible participants will visit the body composition laboratory at UABC in Tijuana, Mexico, between 7–9 AM. They will assist during 3–5 days before the onset of the trial for pre-intervention tests (electrocardiogram, blood chemistry, and a check-up performed by a certified doctor) and familiarization with the exercise program. The first session will be the beginning of the intervention (Day 0), here, antecubital blood samples will be drawn by an expert clinician into EDTA tubes after overnight fasting, after that, body composition measures will be performed, finally, dietary, psychological, and physical activity questionnaries will be obtained. All procedures will be repeated on days 84, 112, and 196. Standard room temperature and humidity will be checked constantly.

### 2.6. Statistical Methods

Normality and homoscedasticity of variables will be screened by the Shapiro–Wilk and the Levene tests, for each group. The analysis of statistical differences among treatments and time, univariate repeated measures ANOVA with two within-participants (initial and final values), and four inter-participants (treatments) factors will be used. Moreover, basal and post-treatment values will be contrasted by paired *t*-tests. Delta values will be analyzed by one-way ANOVA and Tukey Post-hoc tests (normal distribution and equal variances) and Kruskal-Wallis H and Dunn’s Post-hoc test (non-parametric distribution and unequal variances), with Bonferroni setting for multiple comparisons. Spearman correlations will be run to evaluate the associations among variables. Eventual gen-diet and gen-exercise interactions concerning anthropometric and metabolic outcomes will be assessed by univariate regression analyses. Statistically significance will be set at a *p*-value of 0.05. All statistical analyses will be completed using IBM SPSS package version 23 (SPSS Inc, IBM Company, Chicago, IL, USA) and STATA software (StataCorp, College Station, TX, USA).

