#### 2.2.1. Exercise Program

Participants in the exercise program groups will exercise five days a week. The physical activity program will be conducted in accordance with the American College of Sports Medicine recommendations [23] and will consist of Monday to Friday chair exercises performed during 24 weeks.

The approximate exercise duration will be of 40–50 min. Each exercise session has an initial or warm-up phase of 5–10 min (joint movement exercises to increase body temperature starting with movements of head, upper extremities trunk, hip, and, lower extremities); a main physical conditioning phase of 25–30 min that will consist of developing a personalized circuit of strength exercises of the main muscle groups (arms, shoulder, chest, back, and legs) at moderate intensity (between 3.0 and 6.0 metabolic equivalents of task (METs)) using rating of perceived exertion scale and the Talk Test; finally, a cool-down or relaxation phase of 5–10 min. To define the individual exercise intensities in the main physical conditioning phase, participants will have a training of 3 to 5 days before the beginning of the clinical trial to learn how to use the rating of perceived exertion scale and the Talk Test as markers of exercise training intensity.

Trained personnel will assist older adults to perform the exercise program, including articular flexibility, postural exercises, and proprioception exercises. These activities will be selected according to the individual deterioration and joint stiffness that the participants could present. Researchers are trained in cardiopulmonary resuscitation and the laboratory has the necessary tools and communication channels to carry out emergency procedures if a participant presents any side effect of exercise.

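### Section 2.6 analyses the four treatments as independent groups of people, although the supplement is crossed over and each participant supplies data to two of them

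*Protocol article*

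**What the plan says.** Section 2.2 describes a "randomized, double-blind, counterbalanced, crossover, controlled trial with a 2 × 2 factorial design" and states that "a crossover will be conducted for the supplementation interventions". Exercise is not crossed over: "Inclusion in the exercise program intervention will be decided by each participant", and section 2.2.1 says the programme "will consist of Monday to Friday chair exercises performed during 24 weeks", which equals the two 12-week treatment periods together. On timing, section 2.2 has "The first period of treatment will be carried out for 12 weeks, followed by a four-week wash-out period" and then a second 12 weeks. Section 2.5 sets the first assessment at day 0 and adds "All procedures will be repeated on days 84, 112, and 196".

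Section 2.6 gives the main analysis as "univariate repeated measures ANOVA with two within-participants (initial and final values), and four inter-participants (treatments) factors will be used". Change scores then go to one-way ANOVA with Tukey comparisons or, as the fallback, to "Kruskal-Wallis H and Dunn’s Post-hoc test (non-parametric distribution and unequal variances". The only paired test in the section sets baseline against post-treatment values.

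**The concern.** Each completer takes both supplements under one exercise status and so appears in exactly two of the four treatments. Days 0 and 84 give an initial and a final value in the first period, and days 112 and 196 give the same in the second. The stated model puts time within participants and treatment between participants, which is the layout for a four-arm parallel trial. The change-score tests also assume independent groups. The paired test asks whether people change over a period, not whether the same person changes more on S. maxima than on placebo.

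S. maxima versus placebo is the only randomised contrast, because exercise is self-chosen. The synergy question in the main objective (Introduction) is whether that contrast differs by exercise status. Both are answered within people, and the stated analysis does not use that. With no period term, a difference between the periods goes into the error. If the two sequences end up unequal in size, it also biases the supplement contrast.

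**Working it through.** **The plan's own figure.** Section 2.4 gives at least 52 participants at significance level 0.05 and power 0.85. It states no effect size, standard deviation, correlation or test family, so 52 can be neither reproduced nor refuted. The power of 0.85 serves below only as a reference level.

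**Inputs.** From the article: 52 participants, two periods, an initial and a final value in each, four treatments. Assumed: 26 exercisers and 26 non-exercisers, complete data, a common SD of the period change (set to 1), no period or carry-over effect, a two-sided test, and a correlation ρ between a person's two changes.

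**Standard errors if the 104 changes are pooled as four independent groups of 26.**

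- Supplement effect: the planned variance is 2/52. The true variance, from 52 within-person differences each with variance 2(1−ρ), is 2(1−ρ)/52. Planned/true SE = 1/√(1−ρ).
- Supplement effect within one exercise stratum: 2/26 against 2(1−ρ)/26, the same ratio.
- Synergy (supplement × exercise): 4/26 against 4(1−ρ)/26, the same ratio.
- Exercise main effect, if anyone extracts it: each person's average change has variance (1+ρ)/2, so the difference between two groups of 26 has variance (1+ρ)/26 = 2(1+ρ)/52, against a planned 2/52. Planned/true SE = 1/√(1+ρ).
- Pairwise contrasts between different people, such as exercise plus S. maxima against control: no shared participants, so the SE is right.

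**Power and type I error.** The effect d (in SDs of change) is set so that a within-person t test on 49 df has power 0.85: d = 0.599, 0.502, 0.424 and 0.328 at ρ = 0, 0.3, 0.5 and 0.7. The pooled ANOVA has 100 error df and critical value 1.984. Simulation with 20,000 runs per ρ gives:

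| ρ (assumed) | SE ratio, supplement and synergy | Supplement type I error | Supplement power, pooled | SE ratio, exercise | Exercise type I error |
|---|---|---|---|---|---|
| 0 | 1.00 | 0.050 | 0.86 | 1.00 | 0.052 |
| 0.3 | 1.20 | 0.021 | 0.75 | 0.88 | 0.084 |
| 0.5 | 1.41 | 0.006 | 0.61 | 0.82 | 0.107 |
| 0.7 | 1.83 | 0.001 | 0.30 | 0.77 | 0.129 |

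Hand check at ρ = 0.5: 0.424/√(2/52) = 2.16; (2.16 − 1.984)/√0.5 = 0.25; Φ(0.25) = 0.60, against 0.61 simulated. The type I error of the synergy test is 0.020, 0.006 and 0.001 at ρ = 0.3, 0.5 and 0.7. Contrasts between different people stay at about 0.05 throughout. At ρ = −0.25 the directions reverse: supplement 0.080, exercise 0.024.

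**If the ANOVA is run separately in each period.** Each person is then in one group, and the SEs are valid. The supplement comparison is 26 against 26 with variance 2/26, which is 2/(1−ρ) times the within-person variance (4-fold at ρ = 0.5). At d = 0.5 its power is 0.42, against 0.85 (ρ = 0.3) or 0.94 (ρ = 0.5) for the within-person analysis.

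**The case against.** The strongest defence is that section 2.6 never says the two periods are pooled. Run by period, the stated ANOVA is valid, and section 2.2 gives checking compliance, not a within-person efficacy comparison, as the reason for the crossover. This stands in part: pooling is one reading, and the figures in the table belong to that reading alone. But the article does not state a by-period analysis either, and that reading leaves the within-person data of a declared crossover unused.

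A reader might infer that most of the crossover's power is lost. The article does not support that. The loss depends on ρ, which is not given: nil at ρ = 0, about 10 points at 0.3, 24 at 0.5 and 55 at 0.7. The relevant ρ is between two change scores, each with its own baseline, so it may be modest. The initial-to-final comparison already removes stable differences in level between people; only variation in change between people stays in the error.

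A reader might also infer that a planned exercise test is too liberal. Section 2.6 names one four-level treatment factor with post-hoc comparisons, not an exercise main effect. The 8% to 13% error applies only if such an effect is computed from the pooled data.

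An unseen analysis plan does not settle the matter. The article names a model, and the model does not match its own design.

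**Conclusion.** The mismatch between design and analysis is certain from the text: treatment is a between-participant factor in section 2.6 and, for the supplement, a within-participant factor in section 2.2. Its size is not certain. With pooling and positive ρ, the tests of the supplement within an exercise stratum and of synergy are conservative, and power falls from 0.85 to about 0.75, 0.61 and 0.30 at assumed ρ of 0.3, 0.5 and 0.7. At ρ = 0 nothing is lost, and negative ρ makes these tests liberal. With separate periods there is no validity problem, only lost efficiency. These figures rest on a 26/26 split, complete data and no period effect, none of which the article establishes. Under either reading, the one randomised comparison is not made within the person, so section 2.6 should be corrected before analysis.

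**What to change.** In section 2.6, replace the between-participant ANOVA and Kruskal-Wallis comparisons with one linear mixed model per outcome. The response is the change within each period (day 0 to 84 and day 112 to 196) or the period-end value adjusted for that period's baseline; the section should say which. Include a participant random effect and fixed effects for supplement, period, sequence, exercise status and supplement × exercise. Take the S. maxima minus placebo contrast and the synergy contrast from the within-participant comparison. If residuals are clearly non-normal, use a transformation or a within-participant rank or permutation test, so that the pairing is kept.

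The cost is a rewording of section 2.6. The mixed model runs in the SPSS and Stata packages already named, and it needs no new assessments or participants.

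### Section 2.6 adds baseline-versus-post paired t-tests at the same 0.05 threshold as the between-treatment tests and does not rank them below, although they cannot address S. maxima against placebo

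*Protocol article*

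**What the plan says.** Section 2.6 of the protocol article sets out three layers of testing for treatment effects.

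- **Among treatments and over time:** "univariate repeated measures ANOVA with two within-participants (initial and final values), and four inter-participants (treatments) factors will be used".
- **Before against after:** "basal and post-treatment values will be contrasted by paired" *t*-tests. The sentence is an addition to the ANOVA. The natural reading is one test per treatment, although the text does not say so outright.
- **Change scores among treatments:** "Delta values will be analyzed by one-way ANOVA and Tukey Post-hoc tests", or Kruskal-Wallis with Dunn's test where the assumptions fail, "with Bonferroni setting for multiple comparisons".

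One threshold closes the paragraph: "Statistically significance will be set at a *p*-value of 0.05". Nothing says which layer prevails if they disagree.

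The Introduction hypothesises that *S. maxima*, alone or with exercise, "will decrease the body fat percentage and blood lipids while increasing physical function in sedentary elderly patients". The main objective, in the next sentence, names placebo as the comparator. Section 2.2 leaves the exercise programme to each participant's choice; only the supplement is randomised, and it is crossed over.

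**The concern.** A baseline-to-post test in one arm contains no placebo comparison. Its result combines the supplement effect with the passage of time, season, repeated measurement, attention and placebo response. In the exercise groups it also contains the exercise effect, which the Introduction expects to lower adiposity and serum lipids, and whatever distinguishes the people who chose to exercise.

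Because the hypothesis is phrased as a decrease or an increase, a significant paired test can look like confirmation even if the placebo arm changed just as much. The paired tests share the 0.05 threshold and have no stated lower rank, so the plan leaves room to report them as evidence. They also add tests: four treatments for each outcome, with three primary body composition variables and a long secondary list.

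**Working it through.** **The plan's own figure.** Section 2.4 states a "level of significance of 0.05 with a study power of 0.85, selecting a sample of ≥52 participants". The article gives no effect size, SD, correlation or test family, so 52 cannot be reproduced from its own inputs. Nothing below depends on how 52 was obtained.

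**Inputs**
- Total 52 (section 2.4) and four treatments (section 2.2).
- Allocation such that "each group had almost the same proportion of *S. maxima*:placebo (1:1) supplemented individuals" (section 2.4).
- Assumption: exercise choice splits evenly. Then 52 / 4 = 13 per treatment in one period. If both periods are pooled within an exercise stratum, 52 / 2 = 26 per supplement.
- Level 0.05 (section 2.6); two-sided is assumed.
- Assumption: the standardised true change *d* (mean change divided by the SD of change) is the same under *S. maxima* and placebo, so the supplement effect is zero. The article gives no SD or expected change, so a range is shown.
- Assumption, relaxed below: the two arms are independent.

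**Formulas.** Let *p* be the power of a paired *t*-test with *n* participants at *d*, from the noncentral F distribution with 1 and *n* − 1 degrees of freedom and noncentrality *nd*².
- *S. maxima* significant, placebo not: *p*(1 − *p*).
- The two arms disagree in either direction: 2*p*(1 − *p*).

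| *n* per arm | *d* | *p* | *S. maxima* only | Either direction |
|---|---|---|---|---|
| 13 | 0 | 0.050 | 4.8% | 9.5% |
| 13 | 0.2 | 0.102 | 9.2% | 18% |
| 13 | 0.4 | 0.264 | 19% | 39% |
| 13 | 0.6 | 0.512 | 25% | 50% |
| 13 | 0.8 | 0.754 | 19% | 37% |
| 13 | 1.0 | 0.911 | 8.1% | 16% |
| 26 | 0.2 | 0.165 | 14% | 28% |
| 26 | 0.4 | 0.500 | 25% | 50% |
| 26 | 0.6 | 0.836 | 14% | 27% |
| 26 | 1.0 | 0.998 | 0.2% | 0.3% |

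Worked line for *n* = 13, *d* = 0.6: 0.512 × 0.488 = 0.250, and twice that is 0.500. This is the ceiling, because *p*(1 − *p*) cannot exceed 0.25. Beyond *d* = 1.0 both arms are nearly always significant and disagreement fades.

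**Direct comparison.** In simulations of 100,000 trials each, with *d* from 0 to 1.0 and 13 or 26 per arm, a two-sample *t*-test of the change scores kept its type I error at 4.9% to 5.2%.

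**Correlation between periods.** If both periods are pooled, the same people contribute to both arms. Simulated with *n* = 26 and *d* = 0.4, disagreement in either direction is 59% at a correlation of −0.3 between the two changes, 50% at 0, 34% at 0.5 and 26% at 0.7. The one-directional figure is half of each.

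**Multiplicity.** If nothing changes in any arm, four independent unadjusted tests of one outcome give 1 − 0.95⁴ = 18.5%. Over the three primary variables, treated as independent, 1 − 0.95¹² = 46%. Fat percentage, muscle percentage and BMI are related, so the 46% is only a rough guide.

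**The case against.** The strongest reply is that the paired tests do not stand alone. The same section plans an ANOVA across treatments and time and a comparison of change scores among treatments, and both address differences between treatments. Reporting within-group change beside them is common practice. This stands, and it keeps the point modest: the paired tests are a supplement to the inference. What remains is that nothing ranks them below the other tests.

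Three stronger readings are tempting, and the article does not support them.

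- **That the sponsor intends to conclude from significance in one arm and its absence in the other.** Section 2.6 never proposes this. The plan leaves it open; it does not adopt it.
- **That the hypothesis lacks a comparator.** The hypothesis sentence places itself in a controlled trial and the objective that follows names placebo. Rewording would be editorial.
- **That all four arms should agree when the supplement is inert.** A count of disagreement across four arms would need equal change with and without exercise. Exercise is a separate, self-chosen intervention expected to have its own effect, so disagreement across that divide is no false signal about the supplement.

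It is also fair to say that the size rests on an assumed standardised change, that 50% is the arithmetical maximum, and that only half of the disagreement flatters *S. maxima*. On multiplicity, a Bonferroni setting does exist. By position it belongs to the change-score tests, and whether it reaches the paired tests is unclear.

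**Conclusion.** The point holds as a defect of labelling and ranking within an analysis section that already contains between-treatment tests. The paired tests cannot answer the stated objective, yet they carry the same threshold as the tests that are meant to.

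With an inert supplement, 13 per arm and independent arms, the misleading pattern in favour of *S. maxima* arises in about 5% to 25% of trials per outcome for a shared standardised change between 0 and 1.0; disagreement in either direction is 9.5% to 50%. It is rarer if the shared change is larger than that. Positive correlation between a participant's two periods lowers these rates and negative correlation raises them. The 18.5% for four paired tests of one outcome assumes no true change, independent tests and no adjustment.

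This should be corrected before analysis, but it does not invalidate the plan.

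**What to change.** In section 2.6, replace the paired-test sentence. Report the mean change with its 95% confidence interval for each treatment as description only, without hypothesis tests. State that claims about *S. maxima* rest on the *S. maxima* minus placebo difference in change, estimated within participants across the crossover with a term for period, overall and by exercise stratum.

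Rewording the hypothesis to repeat the placebo comparator is optional.

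The cost is a change of text: no visit, measurement or participant is added. The sponsor gives up within-arm *p*-values that do not bear on the objective.
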